### 9.5. Additional information recorded at the selection/inclusion visit

- Patient smoking habits.
- Patient physical examination.
- Patient medical and surgical history.
- History of type 2 Diabetes.
- History of sulfonylurea therapy.
- Waist circumference.

### 9.6. Participant withdrawal criteria

#### 9.6.1. Withdrawal criteria

Premature discontinuation of treatment, does not necessarily mean that the patient prematurely stops the participation in the study. Information to be collected during the follow-up of these participants is given in section 9.6.2. These follow-up modalities are used to insure the efficacy and safety evaluation of all patients who received the study drug.

The reasons for premature discontinuation of treatment are:

- **Adverse events or any condition incompatible with continuation of either treatment** according to the judgement of the investigator or for which the continuation of the study is recommended (refer to the investigator's brochure of benfluorex and pioglitazone monography in appendices 5 and 6). These include:
  - **Hypoglycaemia incompatible with treatment continuation**, e.g. occurrence of one episode of severe hypoglycaemia or repeated non severe hypoglycaemia (> 3 per month) if the sulfonylurea dose can not be decreased anymore.
  - **ALAT increase > 3 times the ULN value**, after 2 consecutive tests performed in 7 days apart (see appendix 5).
  - **Cardiac failure** (see appendix 10).
  - **Clinically significant anaemia** defined by an haemoglobin level < 12g/dL in men and < 11g/dL in women and a decrease  $\geq 1.5$  g/dL in men and  $\geq 1$  g/dL in women (see appendix 12).

- **Major deviation to protocol incompatible with continuation of either treatment** (including pregnancy).
- **Treatment failure (lack of efficacy) defined as uncontrolled metabolic state with:**
  - **HbA1c > 9.5% at W16 or HbA1c > 9% at W28 or W40** unless increase to dose level B is still possible. If external factors (poor compliance, change of diet and lifestyle, occurrence of infectious or inflammatory disease, intake of corticosteroids) are detected, the investigator will reinforce diet advice and recommendations about treatment intake and/or study protocol compliance. At the following study visit, if the HbA1c is still > 9% the study treatment will be stopped.
  - **or hyperglycaemia** unexplained by external factors and confirmed by either:
    - o clinical symptoms (thirst, polyuria,...) and FPG  $\geq$  13.9 mmol/L
    - o or no symptom and FPG  $\geq$  13.9 mmol/L at 2 consecutive measurements separated by an interval of 2 to 4 weeks.
- **Any medical event requiring administration of an unauthorised concomitant treatment** (see paragraph 10.3).
- **Non-medical reason** (to be carefully described).
- **Lost to follow-up:** when the investigator has no news of the participant, he/she must make every effort to contact him/her, to establish the reason for the discontinuation of treatment, and to suggest the participant for coming to an end-of-study visit. If all these attempts to contact the participant fail, the investigator can then declare the participant “lost to follow-up”. The investigator should document all these attempts in the corresponding medical file.

In cases corresponding to the above, the study treatment will be stopped and the investigator will be responsible to take all the appropriate therapeutic measures to control the glycaemic level.

### 9.6.2. Procedure

The investigator must record the reason(s) and the exact date of premature discontinuation of treatment in the case report form.

If more than one reason is given, the investigator must indicate the main reason.

The following data must be collected and recorded in the CRF during the withdrawal visit with a priority order (1 to 5):

- Main evaluation criterion: **HbA1c** sampling for the last value under treatment should be performed **before** stopping the study treatment and if not possible as soon as possible within 10 days after stopping the study treatment.
- **Fasting plasma glucose, serum insulin and lipids** (LDL cholesterol, HDL cholesterol, total cholesterol, triglycerides): sampling should be performed **before** stopping the study treatment to be considered as the last value under treatment and if not possible, as soon as possible after stopping the study treatment.

- **Full physical examination** (including sitting blood pressure, heart rate, body weight, waist circumference), **ECG 12-lead, echocardiography** and **full biology** at the time of premature discontinuation.
- **Adverse events** (including hypoglycaemic episodes), concomitant medications and compliance to the study treatment.
- **Economic outcomes.**

**The investigator will call the IVRS to register the patient with the status “treatment discontinuation”.**

In the case of withdrawal from the study due to an adverse event (event requiring immediate notification or not), the investigator must make every effort to collect the information relating to the outcome of the event. If necessary, the information will be collected afterwards (see section 12.3.1.2.). This information will be recorded in that part of the case report form which concerns adverse events. If the investigator cannot collect the information from a visit, he must collect it from the doctor ensuring the follow-up of the participant.

If the study is stopped or if treatment is discontinued as a result of an event requiring immediate notification, the procedure described in section 12.3.1.3. is to be implemented.

## 10. TREATMENT OF PARTICIPANTS

### 10.1. Treatment administered

Benfluorex, pioglitazone and the placebo will be administered three times per day (from selection to the end of the study): one capsule and one tablet during breakfast, one tablet during lunch and one tablet during dinner.

The usual sulfonylurea treatment will be maintained throughout the study except in case of severe or repeated hypoglycaemia (> 3 episodes in a month). It will not be provided by the Sponsor.

#### ◆ Placebo run-in period (ASSE – W0):

At selection, the patient will continue his/her usual sulfonylurea treatment and will start a placebo run-in period (4 weeks) in order to evaluate the patient compliance.

**At visit ASSE**, all patients will receive one box which will be allocated by the CRO in charge of the IVRS.

#### ◆ Up-Titration period (W0 - W16):

At inclusion, the patient will be randomly assigned to one of the two treatment groups (benfluorex or pioglitazone in addition to his/her usual sulfonylurea) for the double blind comparative period (W0 – W52), which is divided into 2 periods: an up-titration period from W0 to W16 and a dose adaptation period from W16 to the end of the study.

The dose level will be up-titrated in order to reach the optimal dosage for both medications:

**At visit W0**, one box for the period W0-W8 will be allocated by the CRO in charge of IVRS. This box will contain one cartridge “W0” for the period W0-W4 and one box “W4” for the period W4-W8.

**At W0**, all the patients will receive one cartridge containing 2 treatment boxes:

- One box “N°1” (dose I)
- One box “N°2” (dose A)

All patients will start the study treatment with the box N° 1 (dose I). Two weeks after the inclusion visit, the patients will be asked to take the box N° 2 (dose A).

**At W4**, the investigator will give the box “W4” which is corresponding to dose A without calling IVRS.

**At W8**, all the patients will receive a new treatment box which will be allocated by the CRO in charge of the IVRS according to the following rules:

All the patients treated will be adapted according to the FPG value.

The dose will be increased to dose level B if FPG is higher than 7.8 mmol/l except in case of safety concerns.

◆ **Dose adaptation period (W16 - W52):**

**At Visit W16, W28 and Visit W40:** the dose will be adapted according to HbA1c and the safety to obtain the maximal dose tolerated by the patient. If HbA1c is higher than 6.5% at dose A with a good tolerance, the dose will be increased to dose B. At any time during the study and according to safety, the dose can be decreased from dose B to dose A.

The table (10.1) 1 “Description of dose levels and administration schedule” and (10.1) 2 “Criteria for adaptation of study treatments” summarizes the dose levels and administration schedule for both products (benfluorex and pioglitazone) and the criteria for the adaptation of study treatments.

**Table (10.1) 1 - Description of dose levels and administration schedule**

|               | benfluorex group                                                          |                                 |        | pioglitazone group                            |                                 |                                 |
|---------------|---------------------------------------------------------------------------|---------------------------------|--------|-----------------------------------------------|---------------------------------|---------------------------------|
|               | Breakfast                                                                 | Lunch                           | Dinner | Breakfast                                     | Lunch                           | Dinner                          |
| Dose I | benfluorex placebo 
+
pioglitazone placebo  | benfluorex placebo  | 150 mg | benfluorex placebo 
+
30 mg | benfluorex placebo  | benfluorex placebo  |
| Dose A | benfluorex placebo 
+
pioglitazone placebo  | 150 mg                          | 150 mg | benfluorex placebo 
+
30 mg | benfluorex placebo  | benfluorex placebo  |
| Dose B | 150 mg
+
pioglitazone placebo                           | 150 mg                          | 150 mg | benfluorex placebo 
+
45 mg | benfluorex placebo  | benfluorex placebo  |

 A placebo is given temporarily (bid for the dose level I and od for the dose level A) to maintain an administration three times daily during the up-titration period.

 A placebo of the other drug (pioglitazone placebo in the benfluorex group; benfluorex placebo in the pioglitazone group) is given to protect the blind.

Table (10.1) 2 - Criteria for adaptation of study treatments

| Visit                                                    | Criteria                          | Study treatment                                                                                                                                                                                                                                                                                                                     | Sulfonylurea                                                                                                      |
|----------------------------------------------------------|-----------------------------------|-------------------------------------------------------------------------------------------------------------------------------------------------------------------------------------------------------------------------------------------------------------------------------------------------------------------------------------|-------------------------------------------------------------------------------------------------------------------|
| Placebo run-in period (from ASSE to W0)                  |                                   |                                                                                                                                                                                                                                                                                                                                     | Pre-study dose maintained throughout the study except in case of severe or repeated hypoglycaemia (> 3 per month) |
| ASSE                                                     | /                                 | All patients will start with placebo                                                                                                                                                                                                                                                                                                |                                                                                                                   |
| Up-titration period (from W0 to W16)                     |                                   |                                                                                                                                                                                                                                                                                                                                     |                                                                                                                   |
| Adaptation of study treatment to maximal or optimal dose |                                   |                                                                                                                                                                                                                                                                                                                                     |                                                                                                                   |
| W0                                                       | /                                 | All patients will start with dose I (initial).                                                                                                                                                                                                                                                                                      |                                                                                                                   |
| W2
(no visit)                                         | /                                 | All patients will receive dose A.                                                                                                                                                                                                                                                                                                   |                                                                                                                   |
| W4                                                       | /                                 | All patients will receive dose A.                                                                                                                                                                                                                                                                                                   |                                                                                                                   |
| W8                                                       | FPG
Safety                     | If FPG > 7.8 mmol/l: the dose will be increased to dose B, except in case of safety concerns.
Otherwise: the dose is kept constant at dose A.                                                                                                                                                                   |                                                                                                                   |
| Dose adaptation period (from W16 to W52)                 |                                   |                                                                                                                                                                                                                                                                                                                                     |                                                                                                                   |
| W16, W28, W40                                            | Dose increase:
HbA1c
Safety | For the patient receiving dose A:
If HbA1c > 6.5% and no safety concerns: the dose will be increased to dose B.                                                                                                                                                                                                 |                                                                                                                   |
| W16, W28, W40                                            | Dose decrease:
Safety          | For the patient receiving dose A:
In case of major safety concerns: the patient will be withdrawn.
For the patient receiving dose B:
In case of major safety concerns: the dose will be decreased to dose A or the patient will be withdrawn. In case of immediate withdrawal, see appendix 10 |                                                                                                                   |

## 10.2. Treatment dispensing

The treatments will be dispensed at selection (ASSE), at inclusion (W0) and intermediate visits (W4, W8, W16, W28 and W40) by the investigator and/or the pharmacist of the health care institution, after prescription by the investigator or a co-investigator, in accordance with the study plan. Before the dispensing, the investigators must call the IVRS to know the therapeutic unit number for the study treatment except at W4 visit.

For the placebo run-in period, therapeutic unit allocation will be managed by the CRO in charge of the Interactive Voice Response System.

For the double-blind period, randomisation and therapeutic units allocation will be performed under the responsibility of the CRO in charge of IVRS. Treatments will be allocated by non-adaptative, centralised, balanced, stratified randomisation, according to country and HbA1c at W0 ( $\text{HbA1c} \leq 8\%$  or  $\text{HbA1c} > 8\%$ ).

The investigator will be compliant with the IVRS procedures which will be detailed in the user manual provided by IVRS prior to the start of the study.

The investigator should only use the study medication for the patients included in the study. The study medication can also be given by a co-investigator named in the “Organisation of the centre” document under investigator responsibility.

The study treatment will only be dispensed during the study. At the last visit of the study, the investigator will propose a treatment adapted to the nature of the clinical state of the participant.

The detachable portion of the label on the treatment box must be stuck in the case report form by the investigator or on the prescription form if the treatments are dispensed by a pharmacist.

In case of study treatment lost, the patient must immediately inform the investigator who will have to call the IVRS to obtain a new therapeutical unit number.

In case of dose decrease between two visits, the investigator must call the IVRS to obtain a new therapeutic unit number.

### **10.3. Previous and concomitant treatments**

Detailed concomitant treatments are presented in Appendix 7.

#### **Treatments not authorised during the study starting from the selection visit (ASSE) until the last visit (W52).**

- All oral antidiabetic agents other than the usual sulfonylurea prescribed before ASSE authorised according to the selection criteria.
- Insulin : in case of insulin therapy for  $\geq 7$  days, the patient will be withdrawn from the study (contraindicated with glitazones).
- Drugs contraindicated with sulfonylurea (miconazole is an absolute contraindication; please refer to the monography of the prescribed sulfonylurea).

#### **Treatments only allowed for short term use in exceptional cases**

- Oral and injected corticosteroids are not allowed in chronic use. These medications can only be accepted if needed for a short period (10 days maximum) at a distance of at least 1 month from the forthcoming evaluation sampling. If the delay from the evaluation sampling is inferior to one month, this evaluation sampling should be postponed accordingly.

#### **Treatments authorised in chronic use and concomitant treatments**

- Lipid lowering drugs are authorised under conditions (see section 9.2.2).

#### **Special warnings and special precautions for use**

- Concomitant administration of NSAIDs and pioglitazone may increase the risk of oedema and, therefore, should be considered with the greatest precautions.

Details of previous and concomitant treatments should be recorded by the investigator on the appropriate pages, entitled “Concomitant treatments” of the case report form.

#### **10.4. Treatment compliance**

The number of tablets and capsules dispensed and the number of tablets and capsules returned by the participant should be counted by the investigator or a designated person from his/her team and recorded in the case report form.

Each participant must record all new concomitant medication taken between visits with corresponding dates in a diary provided by the investigator.

Compliance will be assessed at the study visits W0, W4, W8, W16, W28, W40 and W52.

#### **10.5. Disease management**

Patient will receive counselling about diabetes, nutrition and physical activity at the selection visit. The prescribed diet should be maintained throughout the study without any modification. He/she will receive information about how to manage hypoglycaemia.

The patient will be provided with a diary card at the selection visit and will be instructed how to use it (e.g. record of any clinically relevant event). This diary is a source document. It must be identified with the name and surname of the patient and kept in the patient's medical file. The patient must return it at each visit and it must be carefully controlled by the investigator.

#### **10.6. Arrangements after the discontinuation of the study treatment**

After the discontinuation of the study treatment, the participant will receive a treatment and/or have access to other appropriate care by his doctor.

## 11. ASSESSMENT OF EFFICACY

### 11.1. Efficacy measurements

Efficacy measurements performed for each visit are indicated in Figure (8.2.2)1 – Investigation schedule. Most of them are biological measurements. They include HbA1c, LDL cholesterol, FPG, fasting plasma insulin, fasting serum lipids (other than LDL cholesterol) and hsCRP.

The waist circumference will be measured.

### 11.2. Methods and measurement times

All efficacy biological measurements will be performed in a central laboratory. Collection and shipment procedures will be specified in a separated document available prior to the start of the study.

The main parameter for the efficacy assessment is the **HbA1c** measurement. It will be assessed at each visit: at W0, W4, W8, W16, W28, W40 and W52. The blood sample (3 mL EDTA vacutainer) should be performed within 7 days before the corresponding visit and HbA1c will be analysed by standardised HPLC method (NGSP certification).

The first secondary criterion is the measurement of LDL cholesterol. It will be performed at each visit: at W0, W4, W8, W16, W28, W40 and W52. The blood sampling should be performed in the morning after at least 8 hours fasting. The dinner preceding this sampling should be light (no fat rich diet, no excess of alcohol).

Blood sampling for the other biological efficacy parameters will be performed in the same conditions as LDL cholesterol: FPG will be assessed at each visit. Fasting plasma insulin will be assessed at baseline and W52. Triglycerides, HDL cholesterol and total cholesterol will be assessed at each visit. Apo A1, Apo B, non-HDL cholesterol will be assessed at W0, W28 and W52, LDL size particle will be assessed at W0 and W52 (and according to countries) and hsCRP will be assessed at W0, W40 and W52.

Throughout the study, the central laboratory results will be transmitted as soon as available to the corresponding investigator, who will keep the original data in the patient file and a copy in the CRF, along with a clinical assessment.

The waist circumference will be measured at W0, W28 and W52 visit. Investigators will be provided a specific device in order to be able to perform this measurement with the same tool during the whole study.

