**Secondary efficacy criteria:**

- LDL cholesterol at each visit.
- FPG at each visit.
- Fasting plasma insulin at W0 and W52 visit (HOMA-IR).
- Other fasting serum lipids:
  - total cholesterol, High Density Lipoprotein (HDL) cholesterol and triglycerides at each visit.
  - Non-HDL cholesterol, Apo A1, Apo B at W0, W28 and W52 visit and LDL particle size (optional) at W0 and W52 visit.
- High sensitive C Reactive Protein (hsCRP) at W0, W40 and W52 visit.
- Waist circumference at W0, W28 and W52 visit.

SAFETY MEASUREMENTS:

- Recording of adverse events (including hypoglycaemia) at each visit.
- Follow-up of cardiovascular events at each visit (Adjudication Committee).
- Centralised biochemistry (including lactic acid assessment at W0 and W52) at W0, W28 and W52 visit.
- Liver parameters follow-up (focusing on ALAT) at W0, W4, W8, W16, W28, W40 and W52 visit.
- Haematology tests at each visit with haemoglobin and haematocrit follow-up.
- NT-proBNP at W0, W028 and W52.
- Physical examination (sitting blood pressure, heart rate, body weight) at each visit.
- Echocardiography (with centralized reading) and 12- lead ECG performed at W0, W52 and in case of suspicion of heart failure.

OTHER:

- Serum library taken at W0 and W52 will be kept at the central laboratory in order to perform further tests in diabetes (no genetic test), its complication markers and safety issues if necessary.
- Economic balance.

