| Adverse events                                      |           | X              | X                   | X              | X              | X                      | X              | X            |
| Suspected hypoglycaemia                             |           | X              | X                   | X              | X              | X                      | X              | X            |
| Concomitant treatments                              | X         | X              | X                   | X              | X              | X                      | X              | X            |
| Allocation of run-in placebo                        | X         |                |                     |                |                |                        |                |              |
| Allocation of study treatments                      |           | X              | X                   | X              | X              | X                      | X              |              |
| Compliance (drug accountability)                    |           | X  | X                   | X              | X              | X                      | X              | X            |
| Economic balance                                    | X         |                |                     |                |                |                        |                | X            |
| Sample library                                      |           | X              |                     |                |                |                        |                | X            |

 Cardiological examination performed by a cardiologist including 12-lead ECG and Doppler Echocardiography (with central reading) for W0, at W52 and in case of suspicion of heart failure.

 Lipids: total cholesterol, LDL cholesterol, HDL cholesterol, triglycerides, non-HDL cholesterol, Apo A1 and Apo B.

 Only total cholesterol, LDL cholesterol, HDL cholesterol, triglycerides.

 Standard biology: complete blood cells count, red blood cell indexes, differential cell count with blood smears, platelet count, total proteins, creatinine, albumin, sodium, potassium, chloride, total bilirubin, ALAT, ASAT,  $\gamma$ -GT, alkaline phosphatase.

 Haematology and liver enzymes (ALAT, ASAT,  $\gamma$ -GT - according to the recommendations, if ALAT > 3 times the upper normal limit, see procedure to follow in section 12.2. "Methods and measurements times".)

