#### **Full Analysis Set (FAS)**

Based on the intention-to-treat principle, this set will correspond to randomised patients who have taken at least one dose of study treatment and who have at least one baseline value and one post-baseline value of HbA1c.

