#### Main analysis:

The main analysis will test the non-inferiority of benfluorex to pioglitazone on the change from baseline value to last post-baseline value using a general linear model studying treatment effect with baseline and country as covariates. The estimate of treatment difference, its standard error and its 95% confidence interval will be provided.

The non-inferiority limit will be set at 0.4%. If non-inferiority is demonstrated, the superiority of benfluorex to pioglitazone will be tested.

In case of sufficient number of centers with minimal number of patients, a mixed model with center as random factor will be used as sensitivity analysis.

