#### Secondary analyses:

- Secondary criteria

The same model as for the main analysis will be performed (estimate of treatment difference, standard error and 95% confidence interval will be provided). A non-parametric approach could be used if necessary.

For LDL cholesterol, superiority of benfluorex to pioglitazone will be tested.

The responder rates on main criteria will be compared using a definition of responders to be defined in the statistical plan (current definition at time of analysis).

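### As written, non-HDL cholesterol is scheduled at three visits only, although total and HDL cholesterol, from which it is calculated, are measured at every visit and at withdrawal

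*Protocol*

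**What the plan says.** Non-HDL cholesterol is a named secondary efficacy criterion (section 14.1.1). Its schedule is given consistently in three places:

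- Synopsis, secondary efficacy criteria: "Non-HDL cholesterol, Apo A1, Apo B at W0, W28 and W52 visit".
- Section 11.2: "Apo A1, Apo B, non-HDL cholesterol will be assessed at W0, W28 and W52".
- Section 8.2.2, investigation schedule: footnote 2 lists non-HDL cholesterol among the full set of fasting lipids. Footnote 3, which applies at W4, W8, W16 and W40, reads "Only total cholesterol, LDL cholesterol, HDL cholesterol, triglycerides".

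The components are collected more often. Section 11.2 says "Triglycerides, HDL cholesterol and total cholesterol will be assessed at each visit". For premature discontinuation, section 9.6.2 asks for a fasting lipid sample and names "LDL cholesterol, HDL cholesterol, total cholesterol, triglycerides".

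On analysis, section 14.1.4 says of the secondary criteria: "The same model as for the main analysis will be performed". The main analysis is of the "change from baseline value to last post-baseline value using a general linear model", primarily in the Full Analysis Set (FAS). Apart from randomisation and at least one dose of study treatment, the FAS takes patients "who have at least one baseline value and one post-baseline value of HbA1c". HbA1c is first measured after baseline at W4, so a patient can enter the FAS from W4 onwards.

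**The concern.** Non-HDL cholesterol needs no assay of its own once total and HDL cholesterol are known, yet the protocol schedules it as sparsely as Apo A1 and Apo B, which do. In a last-value analysis the schedule decides who contributes and from which visit. Followed literally, it has two effects:

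- FAS patients with no sample at W28 or later have no scheduled post-baseline non-HDL value, although total and HDL cholesterol will normally have been measured in them.
- Patients who leave between W28 and W52 may contribute W28 for non-HDL, but W40 or the withdrawal value for total and HDL cholesterol.

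The non-HDL result would then rest on fewer patients, and partly on other time points, than the results for its own components. Leaving before W28 need not be unrelated to outcome. Section 9.6.1 lists adverse events, confirmed hyperglycaemia and (with exceptions) high HbA1c at W16 among the reasons for stopping treatment.

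**Working it through.** **1. The plan's own figure.** No calculation is given for non-HDL cholesterol. The only sample size (section 14.2) is for HbA1c: SD 1.5, margin 0.40, one-sided 2.5%, power 95%, 479 per group. With a true difference of 0.05 against benfluorex, n = 2 × 1.5² × (1.960 + 1.645)² / (0.40 − 0.05)², which is 478 after rounding up; the t-test version gives 479. The figure is reproduced, and nothing below depends on it.

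**2. Schedules side by side** (synopsis, sections 8.2.2, 9.6.2 and 11.2).

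| Visit | Total and HDL cholesterol | Non-HDL cholesterol as scheduled |
|---|---|---|
| W0 | yes | yes |
| W4 | yes | no |
| W8 | yes | no |
| W16 | yes | no |
| W28 | yes | yes |
| W40 | yes | no |
| W52 | yes | yes |
| Withdrawal | yes | not named |

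Both components are scheduled at 7 of 7 visits and non-HDL at 3 of 7. Between baseline and W28 there are three scheduled visits with both components (W4, W8, W16) and none with non-HDL.

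**3. What the last-value rule then picks, on a literal reading.**

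- Patient leaving after W16 and before W28: total and HDL use W16 or the withdrawal sample; non-HDL has nothing.
- Patient leaving after W40 and before W52: total and HDL use W40 or the withdrawal sample; non-HDL uses W28.
- Patient completing W52: all three use W52.

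If the same patients and visits were used throughout, the mean change in non-HDL would equal the mean change in total minus the mean change in HDL. The first two cases break that identity.

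**4. Size.** The protocol gives no dropout rate. Let x be the share of patients with no sample at W28 or later. Assume the same share in both groups and an unchanged residual SD. The standard error is then multiplied by 1/√(1 − x).

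| x (assumed) | Patients of 1000 | 1/√(1 − x) | Rise in standard error |
|---|---|---|---|
| 5% | 50 | 1.026 | 2.6% |
| 10% | 100 | 1.054 | 5.4% |
| 15% | 150 | 1.085 | 8.5% |

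The counts use all 1000 planned inclusions. With the 950 analysed patients of the synopsis, 15% is about 142; with the 975 of section 14.2, about 146. The multiplier does not change. For a given x these are upper bounds: they assume that no early leaver has a non-HDL value from the withdrawal visit, and that every one would have usable total and HDL values.

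**The case against.** The strongest reply is that nothing is lost. Both components are collected, the protocol nowhere forbids subtracting one from the other at W4, W8, W16, W40 or withdrawal, and derivation rules normally belong in the statistical analysis plan, which is not shown. This stands in part. A reader might infer that the protocol excludes early leavers from the non-HDL analysis; it does not go that far, and the loss follows only if the stated schedule is carried into the analysis. But the point is not a missing rule. The protocol states a restrictive schedule in three places, and section 14.1 says the analysis plan will follow the protocol's principal features.

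Second, section 9.6.2 also requires a full laboratory work-up at discontinuation without defining it, and this could include non-HDL cholesterol. Some doubt remains. However, the lipids are listed separately there without non-HDL. The standard laboratory panel in the footnotes of section 8.2.2 contains no lipids, nor do the tests that section 12.2 lists for premature discontinuation.

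Third, section 14.1.1 attaches the last-value variable to HbA1c, and section 14.1.4 carries over only the model to the secondary criteria. Taking the same variable for non-HDL is the natural reading, but it is a reading.

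Fourth, a reader might infer a completers-only or biased comparison. Neither is shown: a patient needs to reach only W28, about the midpoint, and no document figure gives the size or direction of any bias.

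**Conclusion.** The point holds as a consequence of the wording and as a free improvement, not as an error that damages the trial. The protocol schedules non-HDL cholesterol at W0, W28 and W52 although the data to calculate it exist at every visit and at withdrawal. If that schedule governs the last-value analysis, patients leaving before W28 are absent for this criterion, and some who leave later contribute an older value than for total and HDL cholesterol. Under an assumed 5% to 15% leaving before W28, the cost in precision is at most about 2.6% to 8.5% on the standard error. Only this one secondary criterion is touched. The HbA1c tests, the LDL cholesterol superiority test and the sample size are not.

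**What to change.** State in the synopsis, in section 11.2 and in the footnotes to the investigation schedule that non-HDL cholesterol is derived as total minus HDL cholesterol at every visit where both are available, including the withdrawal visit. Add that its analysis uses the same last post-baseline value as the other lipids measured at each visit. Leave Apo A1 and Apo B at W0, W28 and W52, since they need their own assays and the argument does not extend to them.

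The cost is a few words in three places and one derived variable in the analysis data set. No extra blood, visit or assay is needed.
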